### Interim analyses {21b}

In the context of the current study, which primarily aims to evaluate the effectiveness of different sequences of interventions to reduce HbA1c levels, the necessity of conducting interim analyses is recognized. These analyses are crucial for ensuring the quality and consistency of our data, as well as for assessing the fidelity and appropriateness of the interventions being implemented.

At the 6-month mark of our study, we plan to conduct an interim analysis. The objectives of this analysis are multifaceted. Firstly, we aim to assess the quality and consistency of the data being collected across different sites and interventions, ensuring that any discrepancies or issues are identified and addressed promptly. Secondly, we intend to gain an early understanding of the fidelity of the interventions, including DSMT attendance, RGM uptake and adherence, and CHW support. Additionally, we will evaluate the appropriateness of the interventions from the perspectives of both providers and patients, ensuring that the interventions are well-received and fit the needs of the target population.

The interim analysis will be conducted using predefined decision rules to ensure rigor and minimize bias. For data quality and consistency, we will review completeness, accuracy, and consistency of the collected data. Any discrepancies will be addressed by revising data collection procedures and providing additional training to data collectors if necessary. To evaluate fidelity, we will calculate adherence rates to each intervention component. If fidelity rates fall below predefined thresholds (e.g., < 75% attendance for DSMT, < 50% RGM data uploads), we will implement corrective actions such as protocol modifications or enhanced participant engagement strategies.

The process of conducting the interim analysis is designed to be rigorous and unbiased. This will be achieved through several measures. Firstly, the interim analysis will be conducted by a subgroup of the research team that includes experts in biostatistics who are not involved in the day-to-day data collection or intervention delivery, ensuring that the analysis is conducted independently and objectively. To prevent bias, the data analysts will be blinded to the specific intervention groups when feasible, helping to ensure that the analysis and interpretation of the data are not influenced by preconceived expectations about the outcomes of the interventions. Additionally, all data collection and analysis procedures will follow standardized protocols to ensure consistency and reliability, with any deviations from the protocol being documented and addressed systematically. The criteria for making any modifications to the study based on interim analysis findings will be predefined, including specific thresholds for data quality, fidelity, and appropriateness metrics that will trigger corrective actions. By adhering to these predefined rules, we minimize the risk of bias that could arise from ad hoc decision-making. Finally, all steps of the interim analysis, including the decision-making process and any modifications implemented, will be thoroughly documented to ensure transparency.

### Methods for additional analyses (e.g., subgroup analyses) {20b}

In our additional analyses, we aim to explore the potential moderating effects of various demographic and socioeconomic factors on the effectiveness of our stepped-care TBC intervention. Specifically, we will conduct subgroup analyses to investigate whether the impact of the intervention varies across different levels of Race/ethnicity, Age, Sex, and Insurance status. We will employ interaction terms in our regression models to test for statistical interactions between the treatment conditions and these covariates. This will help us to identify any differential effects of the intervention across various subgroups, providing insights into the equity of our intervention and highlighting any potential disparities in its effectiveness. For instance, we will include interaction terms between the treatment conditions and Race/ethnicity to assess whether the intervention’s impact on HbA1c reduction differs between Black/Latine patients and other racial/ethnic groups. Similarly, we will investigate potential age and sex interactions to explore whether the intervention is more or less effective in older versus younger patients, and in male versus female patients.

### Methods in analysis to handle protocol non-adherence and any statistical methods to handle missing data {20c}

In order to address potential issues related to protocol non-adherence in our SMART design, we will employ specialized analytical methods that are tailored to adaptive interventions. Unlike traditional clinical trials where intention-to-treat (ITT) and per-protocol (PP) analyses are commonly used, our study’s design necessitates a different approach due to the planned adaptability of the interventions based on participants’ responses.

We will utilize Q-learning and g-estimation strategies to analyze the primary and secondary outcomes. These methods are specifically designed for adaptive interventions and will allow us to estimate the causal effects of the different sequences of treatments while accounting for the adaptive nature of the intervention. By employing these methods, we aim to obtain unbiased estimates of treatment effects, even in the presence of protocol non-adherence due to the adaptive design.

To handle missing data, we will implement multiple imputation (MI) techniques using a fully conditional specification (FCS) approach, also known as multiple imputation by chained equations (MICE). The imputation model will include variables predictive of the missing values and outcomes, such as baseline HbA1c, age, sex, race/ethnicity, intervention group, and socioeconomic status. Imputation will be performed separately within each treatment arm to account for differences in data distributions, generating 20 imputed datasets to ensure stability and reliability. Each imputed dataset will be analyzed using the specified statistical models for primary and secondary outcomes, including one-way ANOVA, linear regression models, and Q-learning algorithms. The results from the imputed datasets will be combined using Rubin’s rules to produce valid statistical inferences accounting for the uncertainty due to missing data.

To validate the imputation model, we will compare the distribution of imputed values with observed values. Sensitivity analyses will be conducted to assess the robustness of our findings under different missing data mechanisms, comparing results from multiple imputation with those obtained from complete-case analyses and other missing data approaches. This approach aims to ensure accurate and reliable estimates, maintaining the validity of our study’s findings.

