### Intervention description {11a}

In the first randomization, study participants will be randomly assigned to either the DSMT or RGM study arms after completion of the enrollment and baseline data collection. At 6 months, they will attend an in-person appointment for HbA1c lab work (if it has been more than 3 months since their last HbA1c lab work) or HbA1c point of care testing. Depending on their HbA1c, they will continue in the first randomization arm, or they will be rerandomized. Each intervention is described below.

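### Section {20c} sets intention-to-treat aside because the interventions adapt by plan, although analysis by assignment is fully available in a SMART, and it leaves participants lost before month 6 without a place in the six-condition ANOVA

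*Protocol article*

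**What the plan says.** All references are to the protocol article.

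- **Ground for departing from intention-to-treat, section {20c}.** Intention-to-treat and per-protocol are described as the approach of conventional trials. This trial's "design necessitates a different approach due to the planned adaptability of the interventions".
- **Replacement, section {20c}.** "We will utilize Q-learning and g-estimation strategies to analyze the primary and secondary outcomes". The stated hope is that "we aim to obtain unbiased estimates of treatment effects, even in the presence of protocol non-adherence due to the adaptive design".
- **Missing data, section {20c}.** Multiple imputation by chained equations, 20 datasets. "Imputation will be performed separately within each treatment arm to account for differences in data distributions". The predictors are given as examples: "such as baseline HbA1c, age, sex, race/ethnicity, intervention group, and socioeconomic status". Each imputed dataset then goes into the outcome models, "including one-way ANOVA, linear regression models, and Q-learning algorithms".
- **Comparison groups, Sample size {14} and Primary outcomes under {20a}.** The groups compared are the six treatment conditions, on HbA1c change from baseline to 12 months.
- **How a condition arises, Intervention description {11a}.** After the 6-month visit: "Depending on their HbA1c, they will continue in the first randomization arm, or they will be rerandomized".

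**The concern.** Two things in section {20c} do not fit a SMART.

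First, planned re-randomization is treated as if it were a departure from protocol. It is the protocol. Non-adherence in this trial means missed DSMT sessions, readings not uploaded, or CHW contacts not made, which is how Strategies to improve adherence {11c} and the fidelity rows of Table 2 measure it. Rejecting intention-to-treat for the wrong reason leaves the estimand of the primary analysis open and credits the named methods with a protection they do not give on their own.

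Second, a participant's condition does not exist until month 6. Anyone lost earlier has a first-stage arm but no path. Followed literally, the plan makes membership of the six analysed groups depend on staying to month 6. If staying is related to glycaemic course, or differs between DSMT and RGM, the path means and any comparison across first-stage arms describe those who stayed, not those randomized. The comparison of the two second-stage options among participants who were actually re-randomized remains randomized.

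**Working it through.** **1. The plan's own figures.** Inputs from Sample size {14}: six groups, f = 0.25, alpha 5%, power 80%, equal allocation, 20% dropout. For a one-way ANOVA the noncentrality is lambda = N × f². The smallest N with 80% power is 211, and the next multiple of six is 216 (lambda = 216 × 0.0625 = 13.5, power 0.811). Allowing for dropout, 216 / (1 − 0.20) = 270. Both stated figures reproduce, and no figure is disputed here.

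**2. Is analysis by assignment available?** Sequence generation {16a} provides one envelope for stage one, and one for stage two from a box specific to the first assignment. Responders stay in their first arm by rule. So every participant has a randomized assignment at each stage where one is due, and the adaptive step is a known function of the 6-month HbA1c. Nothing in the design stops an analysis by assigned sequence or by embedded regime.

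**3. What the named methods deliver.** Primary outcomes under {20a} describes Q-learning as regression models of the outcome on treatment and covariates.

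- On assigned treatment this is an intention-to-treat type of analysis. It handles the sequential decision and makes no correction for non-uptake.
- On received treatment it would be open to confounding by who adheres.
- G-estimation can address received treatment, but it needs modelled adherence and further assumptions. Section {20c} states neither.

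The two sections also differ on the primary analysis: {20a} names linear regression, with ANOVA for the six condition means, while {20c} gives the primary outcome to Q-learning and g-estimation.

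**4. Where a participant lost before month 6 goes.** Section {20c} does not define *treatment arm*, so both readings are followed through.

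| Reading | Imputation | Six-condition ANOVA |
|---|---|---|
| Six paths | No stratum, because the path is unknown | No group |
| Two initial arms | 6- and 12-month HbA1c can be imputed | An imputed responder has a condition; an imputed non-responder has no second-stage assignment and so no group |

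The gap for non-responders survives on either reading. No section says that response or second-stage assignment will be imputed.

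**5. Size.** The allowance is 0.20 × 270 = 54 participants. Its timing is not given, so a range is shown as an assumption:

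| Share of the 54 lost before month 6 | Without an observed path | With a path |
|---|---|---|
| 0% | 0 | 270 |
| 25% | about 14 | about 256 |
| 50% | 27 | 243 |
| 100% | 54 | 216 |

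With equal groups and f = 0.25, six-group power is 0.90 at 270, 0.86 at 243 and 0.81 at 216. On the plan's own assumptions power is not what suffers.

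**The case against.** The strongest reply is that the randomized comparison has not been given up. A reader might infer from the rejection of intention-to-treat that participants will be analysed by treatment received. The document does not say so. Who will be blinded {17a} has the statistician receive the arms assigned at each randomization point, and Primary outcomes under {20a} defines the Q-function by the treatment assigned. Linear regression and ANOVA by condition are also kept. This stands: the fault is a wrong argument and the lack of a clear statement, not a declared as-treated analysis. The text also words unbiasedness as an aim, not as a claim.

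A reader might also infer that the imputation model leaves out the 6-month HbA1c. The list is introduced by *such as*, the governing rule is to include predictive variables, and {20a} already names 6-month HbA1c as an adjustment covariate. Its omission is not established, and a full predictor list belongs in the analysis plan.

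Nor can the extent of non-adherence be read from Interim analyses {21b}. The sentence beginning "If fidelity rates fall below predefined thresholds" gives example triggers for corrective action. They are not expected rates and are not tied to an effectiveness analysis.

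Finally, *arm* may well mean the two initial arms, in which case early leavers do have an imputation stratum. That narrows the problem to imputed non-responders but does not remove it. Leaving the matter to the analysis plan is only a partial answer, because the rejection of intention-to-treat and imputation by arm are written as settled and would have to be reversed or defined.

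**Conclusion.** The point holds in this form. The reason given for setting intention-to-treat aside is wrong, and the methods put in its place do not in themselves secure unbiased effects under non-adherence. The document points towards analysis by assignment without saying so, and the sentence rejecting intention-to-treat should be replaced. In addition, the plan runs a six-condition ANOVA on imputed data without giving a condition to imputed non-responders lost before month 6, whichever way *treatment arm* is read.

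The number without an observed path lies between 0 and 54 of 270. That range assumes that loss equals the plan's 20% allowance, and its timing is unknown. The harm is selection on staying to month 6, and its direction and size cannot be derived from the document. The change should be made, but it calls for no new sample size and no new data.

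**What to change.** 1. Replace the passage in {20c} that rejects intention-to-treat. State that the primary and secondary effectiveness analyses, including Q-learning, use assignment as randomized at each stage for all randomized participants. Any analysis of treatment received, for example by g-estimation, becomes a sensitivity analysis with its assumptions stated.
2. Define *treatment arm* for imputation as the first-stage arm, and impute in time order:
   - 6-month HbA1c;
   - response, derived from it;
   - for imputed non-responders who were never re-randomized, the second-stage option drawn 1:1, matching the 60 and 60 envelopes in each second-stage box in {16a};
   - 12-month HbA1c, with 6-month HbA1c and second-stage assignment in the model.

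A weighted comparison of the embedded regimes is an acceptable alternative, provided that it also deals with loss before month 6.

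The cost is revised wording and slightly more programming. The effect by assignment may also be smaller than an as-treated one.

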### Sample size {14}

The sample size calculation, performed using G*Power (version 3.1), is based on the primary outcome of HbA1c over the 12-month study period, with the primary predictor being the six treatment conditions taken over the course of the study. The Null (H0) and Alternative (H1) Hypotheses are H0: There is no difference in the mean change in HbA1c among the six treatment groups, and H1: There is a significant difference in the mean change in HbA1c among the six treatment groups. The analysis assumes a significance level of 5%, 80% power, six treatment groups, equal group allocation, and a medium effect size of *f* = 0.25. The effect size of *f* = 0.25 was selected based on Cohen’s conventions for effect sizes in behavioral sciences, where 0.10 represents a small effect, 0.25 represents a medium effect, and 0.40 represents a large effect. A medium effect size is considered appropriate for this study, as it balances the detection of meaningful clinical differences with practical sample size considerations. Previous studies on diabetes management interventions such as DSMT and RGM have reported effect sizes in this range, indicating that a medium effect size is a reasonable expectation for interventions aimed at reducing HbA1c [13, 25].

The sample size estimation properly accounted for the multiple groups and comparisons inherent in the SMART design. Specifically, we conducted the sample size estimation for detecting a difference in HbA1c change across the six treatment groups, using an ANOVA framework, which inherently accounts for multiple comparisons. To ensure robustness and accommodate potential dropouts, we inflated the sample size by 20%. Thus, the minimum required sample size is 216 patients, and to account for an anticipated dropout rate, we aim to recruit 270 patients. This approach ensures that the study is adequately powered to detect significant differences across all treatment conditions, providing a solid basis for our subsequent analyses.

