#### Primary outcomes

To optimize the adaptive intervention and understand the causal effects of each proposed sequence, we will employ a SMART design. This design is particularly advantageous for chronic diseases like diabetes, where there is significant heterogeneity in response to treatment. The SMART design allows for re-randomization based on a tailoring variable, which in our study is the change in HbA1c at 6 months, enabling patients to receive an adaptive intervention that is most suited to their needs. To address potential imbalances in randomization, we will use stratified and block randomization techniques.

For primary analysis, we will employ linear regression models adjusting for baseline characteristics utilizing type III sum of squares to account for these discrepancies. Sensitivity analyses will include inverse probability weighting to account for any imbalances. To assess the overall HbA1c reduction by treatment condition and the average patient percentage point reduction in HbA1c from baseline to 12 months within each of the six treatment conditions, we will utilize one-way ANOVA for mean comparisons, followed by pairwise comparisons with a Tukey post hoc test to correct for multiple comparisons. In cases of non-normal data distribution, we will opt for Kruskall-Wallis tests and a Dunn post hoc test with Hommel multiple comparison *p*-value corrections.

Linear regression will be employed to adjust for additional covariates that may confound the relationship between treatment and outcome, such as baseline characteristics with residual confounding post-randomization, and baseline and 6-month HbA1c values. We will also test for possible interactions of covariates with the treatment variable, reporting model adjusted slopes (β_ADJ_), 95% confidence intervals, model diagnostics, and goodness of fit (via R^2^).

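### The test that was powered, the analysis labelled primary and the methods later assigned to the primary outcome are three different things, and the protocol does not say which one decides the hypothesis

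*Protocol article*

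**What the plan says.** Three sections of the protocol article bear on how 12-month change in HbA1c will be tested.

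- **Sample size {14}.** The null hypothesis is equal mean HbA1c change across six treatment groups. The error rates belong to that test: "The analysis assumes a significance level of 5%, 80% power, six treatment groups, equal group allocation, and a medium effect size of" 0.25. It was done "using an ANOVA framework, which inherently accounts for multiple comparisons". The result is that "the minimum required sample size is 216 patients", with a recruitment target of 270.
- **Primary outcomes, under {20a}.** "For primary analysis, we will employ linear regression models adjusting for baseline characteristics", with type III sums of squares. For the comparison of the six conditions, the same paragraph says "we will utilize one-way ANOVA for mean comparisons, followed by pairwise comparisons with a Tukey post hoc test". Kruskal-Wallis with Dunn replaces ANOVA if the data are not normal. The next paragraph adds a regression that also adjusts for baseline and 6-month HbA1c. Q-learning then has its own stated purpose, finding the optimal dynamic treatment regime.
- **Non-adherence and missing data {20c}.** The design is said to call for an approach other than the usual ones, and "We will utilize Q-learning and g-estimation strategies to analyze the primary and secondary outcomes". After imputation, ANOVA, regression and Q-learning are listed side by side. G-estimation is not in that list.

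The analyses explicitly called sensitivity analyses are inverse probability weighting and the missing-data comparisons.

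**The concern.** The analyses answer different questions. The ANOVA compares unadjusted path means. The regression compares path means given covariates, and its two descriptions differ on whether 6-month HbA1c is among them. Q-learning and g-estimation target regime or stage-specific effects. Tukey controls error among pairwise comparisons inside the ANOVA only, and the omnibus F test controls error for its own global null only.

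Two things are at stake. First, if more than one analysis can support the claim, the 5% level no longer describes the trial. Second, the analyses can disagree, and the protocol gives no rule for settling the null hypothesis in Sample size {14} or the path E hypothesis in Trial design {8}. Disagreement is likely by construction. Responders stay in their first arm and only non-responders are re-randomised, so the six paths are two responder groups and four non-responder groups. Path membership is then partly a result of the patient's own HbA1c course.

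**Working it through.** **1. The plan's own figure.** Inputs from Sample size {14}: f = 0.25, six groups, alpha 5%, power 80%. For a fixed-effects one-way ANOVA the noncentrality is λ = f²N, with 5 and N − 6 degrees of freedom. The smallest N reaching 80% is 211. Rounded up to equal groups this is 6 × 36 = 216, where λ = 0.0625 × 216 = 13.5 and power is 81.1%. For dropout, 216 / (1 − 0.20) = 270. Both figures reproduce. They belong to the unadjusted six-group ANOVA.

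**2. Side by side.**

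| Section | Analysis of HbA1c change | Status given |
|---|---|---|
| Sample size {14} | Unadjusted six-group ANOVA | Carries the 5% and 80% |
| Primary outcomes | Regression on baseline characteristics | Labelled primary |
| Primary outcomes | ANOVA/Tukey, or Kruskal-Wallis/Dunn | Compares the six paths; no rank |
| Primary outcomes | Regression adding baseline and 6-month HbA1c | No rank |
| Item {20c} | Q-learning and g-estimation | Assigned to the primary outcome; no rank |

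**3. Multiplicity, if more than one may decide.** Null simulation with N = 216 and six groups of 36 formed at random. The assumptions, none given in the protocol, are normal data, HbA1c SD 1.7, equal correlation between visits of 0.3, 0.5 or 0.7, and means of 9.0 at baseline and 8.5 at both later visits.

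- ANOVA or baseline-adjusted regression significant at 5%: 6.7–9.3% in sets of 1,500 runs and 6.9–8.5% in sets of 4,000. In round terms this is 7–8%.
- Adding the regression with 6-month HbA1c: 8.5–10.3% in sets of 1,500 runs, about 9% in round terms.
- When at least one of the first two is significant, the other is not in 60–72% of cases.

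**4. Same assumptions, paths formed as the protocol forms them.** A fall of at least one percentage point at 6 months defines a responder. Non-responders are split at random between two options, and there is no treatment effect at either stage. Rejection rates at 5% (1,500 runs each):

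| Visit correlation | Path ANOVA | Path regression, baseline | Path regression, baseline + 6-month | First-stage contrast |
|---|---|---|---|---|
| 0.3 | 99.9% | 41.6% | 5.5% | 4.6% |
| 0.5 | 99.9% | 81.5% | 6.6% | 6.0% |
| 0.7 | 100% | 96.8% | 5.0% | 4.8% |

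Repeat simulations gave the same pattern, with the baseline-adjusted regression ranging from 38% upward. The mechanism is selection. Responders have a large baseline-to-6-month fall by definition, so their 12-month change is larger on average whatever treatment does. Adjusting for baseline removes part of this. Adjusting for 6-month HbA1c removes it under this null, but it also conditions on a result of the first randomisation, so it would hide part of a real first-stage effect.

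**The case against.** A reader might infer that no analysis is designated primary and that the 5% and 80% attach to no test at all. The documents do not support that. Adjusted regression carries the primary label, and the error rates attach to the six-group ANOVA, whose sample size reproduces. Some ranking is also stated, since weighting and the missing-data comparisons are sensitivity analyses.

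It is also fair to say that a linear model with a six-level treatment factor is the adjusted counterpart of the ANOVA, and that sizing on the simpler test and analysing with covariates is common. In an ordinary parallel trial this gap would be minor. Here it is not, because the two give very different rejection rates once the paths are formed by response.

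A reader might reach an inflation figure of 12–18% by counting Kruskal-Wallis and first- and second-stage contrasts as further chances to win. That does not stand. Kruskal-Wallis is a conditional replacement for ANOVA. The stage contrasts are nowhere planned as confirmatory tests. Q-learning is described in the Primary outcomes section as estimating an optimal regime, a separate question.

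The 7–9% figures assume randomly formed groups, so they illustrate multiplicity alone and are not this trial's error rate. That limit stands.

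Finally, the ranking of supportive analyses is commonly left to an analysis plan, which the protocol promises and which is not shown. Missing detail is therefore not the point. The point is that three sections of the published protocol conflict on what tests the primary outcome.

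**Conclusion.** The conflict is real and should be corrected. One test is powered, a different analysis is labelled primary, and a later section gives the primary outcome to two further methods, with no statement of which decides.

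The multiplicity cost is modest: about 7–8%, or about 9% with the third regression, in place of 5%. The larger issue is which analysis is chosen. With no treatment effect, the listed analyses range from near-certain rejection (path ANOVA) through roughly 40% to over 90% (baseline-adjusted path regression) to about 5% (6-month-adjusted regression). The exact rates rest on the assumed SD, means and correlations. The ordering follows from selecting two paths on 6-month HbA1c and held at every correlation tried.

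**What to change.** Reconcile Sample size {14}, Primary outcomes and item {20c}:

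1. Name one primary analysis and one primary contrast for 12-month HbA1c change, comparing options that were randomised or the embedded regimes. One example is a baseline- and site-adjusted weighted comparison of the four embedded regimes (two first-stage arms × two options for non-responders). If both randomisations are 1:1, as the envelope counts imply, the weights are 1/0.5 = 2 for responders and 1/(0.5 × 0.5) = 4 for non-responders, with a robust variance because each responder is consistent with two regimes.
2. State one multiplicity procedure for that analysis, and express the path E hypothesis as a contrast within it.
3. Label path ANOVA or Kruskal-Wallis, path regression, Q-learning and g-estimation as supportive or exploratory. Present path summaries as descriptive.
4. Restate power for the chosen analysis at the planned 270 recruited and 216 evaluable.

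The cost is protocol and analysis-plan wording plus one power calculation. No change to data collection is needed. The downside is that the restated power may be less favourable than the present 80%.
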